### Relevant Concomitant Care Permitted or Prohibited During the Trial

During the preimplementation phase, health care professionals provide aftercare as usual. No other concomitant care or interventions are prohibited during the study.

### Outcomes

#### Overview

To translate our intervention into practice, we adhere to the RE-AIM framework [26,27]. The RE-AIM framework consists of 5 dimensions—reach, effectiveness, adoption, implementation, and maintenance. We have presented each outcome measure under its RE-AIM dimension in Table 1. Detailed information on the definitions of the RE-AIM dimensions and their related measures can be found in Multimedia Appendix 1.

**Table 1. T1:** Overview of the outcome measures categorized by each RE-AIM^a^ dimension.

Outcome	Instrument	Number of questions	Number of domains	Answer scale	Minimum-maximum score
Coprimary outcome effectiveness measure					
Self-management skills	Partners in Health scale [34]	12	2	9-point Likert scale	0‐96
Secondary outcome effectiveness measures – survivor of burn injuries level					
Self-regulation	Self-Regulation Assessment [35]	22	4	5-point Likert scale	0‐110
Participation	Measure of Experiential Aspects of Participation [36]	4	4	5 answer options	—^b^
Daily activities	EuroQol-5D-5L [37]	1	—	5-point Likert scale	1‐5
Self-care	EuroQol-5D-5L [37]	1	—	5-point Likert scale	1‐5
Dependency	New formulated question	1	—	5-point Likert scale	1‐5
Return to work or school	Adjusted International Consortium for Health Outcomes Measurement [38]	3	—	5 answer options	—
Patient centeredness	American Consumer Assessment of Health Plan Survey [39]	5	—	4-point Likert scale	0‐20
Secondary outcome effectiveness measures – health care professional level					
Self-management support skills	Self-Efficacy and Performance in Self-management Support [40]	36	6	5-point Likert scale	0‐180
Need-supportive counseling	Coding and Observing Need-Supportive Counseling in Chronic Care Encounters [41]	44	9	5-point Likert scale	0‐24
	Nurse-Child Interaction Taxonomy [42]	16	3	Percentages	0%‐100%
Secondary outcome effectiveness measures – setting level					
Cost-effectiveness	EuroQol-5D-5L [37]	6	5	5-point Likert scale Visual Analog Scale	5‐25 0‐10
Coprimary outcome implementation approach measures					
Reach	Dutch Burn Repository R3	—	—	Frequencies and percentages	—
Reach	Project coordinator records	—	—	—	—
Reach	Screening form	—	—	—	—
Reach	CFIR^c^-informed interviews	—	—	—	—
Adoption (staff level)	CFIR-informed interviews	—	—	—	—
Adoption (setting level)	Project coordinator records	—	—	—	—
Intervention fidelity	Electronic patient records	—	—	Frequencies and percentages	—
Intervention fidelity	Project coordinator records	—	—	—	—
Intervention fidelity	CFIR-informed interviews	—	—	—	—
Implementation fidelity	Completion of implementation plan	—	—	Frequencies and percentages	—
Implementation adaptations	Framework for Reporting Adaptations and Modifications-Enhanced [43]	—	—	—	—
Maintenance (staff level)	Provider Report of Sustainment Scale [44]	3	—	Frequencies and percentages	—
Maintenance (staff level)	Self-Efficacy and Performance in Self-management Support [40]	36	6	5-point Likert scale	0‐180
Maintenance (staff level)	CFIR-informed interviews	—	—	—	—
Maintenance (setting level)	Clinical Sustainability Assessment Tool [45]	35	7	7-point Likert scale	0‐245
Maintenance (setting level)	CFIR-informed interviews	—	—	—	—

a RE-AIM: Reach, Effectiveness, Adoption, Implementation, and Maintenance.

b Not applicable.

c CFIR: Consolidated Framework for Implementation Research.

#### RE-AIM: Reach

To determine the representativeness of survivors of burn injuries, participant demographics will be compared with those of nonparticipants using the Dutch Burn Repository R3. Nonparticipants will include both survivors of burn injuries who did not meet the eligibility criteria and eligible survivors of burn injuries who declined participation. We will compare some characteristics, such as sex, age, total body surface area burned, operation, and length of stay. Comparisons will be descriptive in nature and will be used to assess the representativeness of the study sample and to explore potential selection effects, rather than to draw causal inferences.

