### Eligibility Criteria

#### Survivors of Burn Injuries

Eligible for inclusion are patients with burns who receive burn aftercare at 1 of the 3 specialized burn centers, who (1) are 18 years of age or older, (2) have been admitted for more than 24 hours or undergoing a wound-management procedure in theater, and (3) have proficiency in the Dutch language, as judged by the treating clinician. Exclusion criteria are cognitive limitations in such a way that self-management skills cannot be learned or executed, an acute psychiatric illness, or being discharged to a different health care institution. Cognitive limitations and acute psychiatric illness will be assessed by the treating clinician based on routine clinical judgment.

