### Data Collection and Management

#### Data Collection Methods

##### Survivors of Burn Injuries

Assessment time points are at discharge, 2 weeks after discharge, and 6 and 12 months after discharge, as pictured in Table 2. Questionnaires at 2 weeks after discharge and 12 months are part of the routinely collected value-based health care burns core set, from the BORN [58]. Participants receive the questionnaires by email. In cases where patients do not have an email address or access to a computer, the questionnaire can be completed by telephone interview or on paper. Using the Dutch Burn Repository R3, the characteristics sex, age, and total burned body surface area will be collected from all eligible survivors of burn injuries during the study period.

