##### RE-AIM: Reach

To examine if participating survivors of burn injuries are representative of the general survivor of burn injuries population, baseline demographics of participating survivors of burn injuries and nonparticipating survivors of burn injuries will be compared using chi-square tests for categorical data, and Mann-Whitney or independent *t* tests for numerical data.

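### The reach comparison pools ineligible patients with eligible decliners, so it cannot separate selection among eligible patients from the effect of the entry criteria, and the data-collection section describes a different extract

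*Protocol article*

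**What the plan says.** Reach is one of the coprimary implementation outcomes (Objectives; Table 1). Under Outcomes, RE-AIM: Reach, participants are compared with nonparticipants from the Dutch Burn Repository R3, and the comparator is defined as follows: "Nonparticipants will include both survivors of burn injuries who did not meet the eligibility criteria and eligible survivors of burn injuries who declined participation". The variables are named next: "We will compare some characteristics, such as sex, age, total body surface area burned, operation, and length of stay". The comparisons are called descriptive and "will be used to assess the representativeness of the study sample and to explore potential selection effects, rather than to draw causal inferences".

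Under Statistical Methods, RE-AIM: Reach, the aim is stated as "To examine if participating survivors of burn injuries are representative of the general survivor of burn injuries population", and "baseline demographics of participating survivors of burn injuries and nonparticipating survivors of burn injuries will be compared using chi-square tests for categorical data", with Mann-Whitney or t tests for numerical variables. There are two groups and no split by eligibility.

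Under Data Collection Methods, Survivors of Burn Injuries, the repository extract is narrower: "the characteristics sex, age, and total burned body surface area will be collected from all eligible survivors of burn injuries during the study period".

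Two further sections bear on the point. Eligibility Criteria admits patients who "are 18 years of age or older", who stayed beyond 24 hours or had a wound procedure in theater, and who have adequate Dutch. It excludes certain cognitive limitations, acute psychiatric illness and discharge to another institution. Data Management, Survivors of Burn Injuries, describes an eligibility file that holds admission, surgery and discharge dates and records whether each eligible patient took part and, if not, why.

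**The concern.** Two questions share one comparator. Whether the sample resembles burn survivors at large is properly asked against everyone who did not take part. Whether the eligible patients who agreed differ from the eligible patients who refused can only be asked among eligible patients. Three of the five named variables (age, operation, length of stay) are the entry criteria or follow closely from them, so patients excluded on those criteria are likely to differ on these variables for that reason alone. A difference in the pooled contrast cannot be attributed to selection, and the absence of one does not rule selection out.

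Selection matters here because control and intervention patients are enrolled in different calendar periods, without randomization or blinding, and the article's Methodological Considerations acknowledge the resulting risk of bias. A reach analysis that appears to address selection but cannot may give false reassurance or a false alarm.

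The second problem is internal consistency. As written, the extract under Data Collection Methods cannot supply the comparison described under Outcomes.

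**Working it through.** The article gives no figure for this comparison, so there is none to reproduce.

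**1. What the pooled contrast estimates.** Let P, D and I be the mean or proportion of a characteristic among participants, eligible decliners and ineligible patients. Let w be the ineligible share of nonparticipants. Then

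pooled contrast = P − [w·I + (1 − w)·D] = (P − D) + w·(D − I).

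The first term is selection among eligible patients. The second is the eligibility effect, weighted by w. One two-group comparison cannot separate them.

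**2. How large w might be.** Inputs from the article: about 1000 admissions a year (Patients With Burns); recruitment from April 2024 to June 30, 2025, about 15 months (Trial Design; Results); 42 + 53 = 95 participants (Results). If every admission is in the frame, A = 1000 × 15/12 = 1250, and nonparticipants number 1250 − 95 = 1155. The participation rate p among eligible patients is not given and is assumed. Treating every eligible nonparticipant as a decliner,

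w = (A − 95/p)/(A − 95).

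The frame may be smaller than all admissions, because only newly referred patients entering aftercare are approached. Assumed frames of half and 30% of admissions are therefore shown as well.

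| Frame A | p = 0.3 | p = 0.5 | p = 0.7 |
|---|---|---|---|
| 1250 | (1250 − 316.7)/1155 = 81% | (1250 − 190)/1155 = 92% | (1250 − 135.7)/1155 = 96% |
| 625 | (625 − 316.7)/530 = 58% | (625 − 190)/530 = 82% | (625 − 135.7)/530 = 92% |
| 375 | (375 − 316.7)/280 = 21% | (375 − 190)/280 = 66% | (375 − 135.7)/280 = 85% |

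If instead the Data Collection Methods sentence governs and only eligible patients are extracted, w = 0.

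**3. What pooling can do.** The operation rates below are assumed for illustration.

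| P | D | I | True P − D | Pooled, w = 0.5 | Pooled, w = 0.8 |
|---|---|---|---|---|---|
| 60% | 60% | 20% | 0 | 0 + 0.5 × 40 = +20 | 0 + 0.8 × 40 = +32 |
| 50% | 30% | 55% | +20 | 20 − 0.5 × 25 = +7.5 | 20 − 0.8 × 25 = 0 |

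The first row creates an apparent selection effect; the second hides a real one.

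**4. Sections side by side.**

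| Section | Groups | Variables |
|---|---|---|
| Outcomes, RE-AIM: Reach | Participants; decliners and ineligible patients together | Sex, age, burned area, operation, length of stay |
| Statistical Methods, RE-AIM: Reach | Participants; nonparticipants | Baseline demographics |
| Data Collection Methods | Eligible patients only | Sex, age, burned area |
| Data Management (eligibility file) | Eligible patients | Admission, surgery and discharge dates; participation and reason |

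The first and third rows cannot both describe the repository extract. The fourth shows that operation and length of stay can be derived for participants and decliners, although from a different source than the Outcomes section names. No section says where these two variables come from for ineligible patients, other than the general reference to R3 under Outcomes.

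**The case against.** The strongest defense is that the pooled group suits the aim given in the statistical section. Against burn survivors at large, ineligible patients belong in the comparator, and differences produced by the entry criteria are part of the answer. That stands, and it is why ineligible patients should stay in the report. It does not cover the second aim, which the Outcomes section states explicitly.

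The definition of nonparticipants also does not forbid showing the two subgroups separately, and a breakdown could be left to a fuller document. That is fair as to detail. But the article does fix the grouping, and its test section carries that grouping forward unsplit.

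Several stronger readings are tempting, and the documents do not support them:

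- A reader might infer that the comparison mainly reflects the entry criteria. The numbers eligible and declining are not given. The ineligible share is high under most of the assumptions above, but only 21% under one of them and zero if only eligible patients are extracted.
- A reader might try to state how often the planned tests would flag a spurious difference. That needs an assumed gap and spread for each variable, and the article gives neither. Even the direction for age is uncertain: minors are excluded, but so are patients with certain cognitive limitations or discharged to another institution.
- A reader might infer that the coprimary reach outcome as a whole fails. Table 1 also draws reach from coordinator records, screening forms and interviews, and the definitions are in Multimedia Appendix 1, which is not shown. Reach as a proportion of eligible patients may be defined there.
- A reader might take this as the trial's principal safeguard against selection. The effectiveness analysis separately compares control and intervention participants at baseline and considers age and sex in the model. That check covers enrolled patients only and says nothing about decliners, but it exists.
- A reader might conclude that operation and length of stay are unavailable. For eligible patients the recorded dates supply them.

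**Conclusion.** The concern holds in a limited form. The pooled comparison can address representativeness for burn survivors in general. It cannot address the other stated purpose, selection effects, because it mixes the eligibility effect with selection among eligible patients in a proportion the documents do not give. The mixing follows from the algebra whenever ineligible patients are included and differ from decliners; its size is unknown. The 32-point and 0-point illustrations rest on assumed rates and w = 0.8, and show only that pooling can create or mask a difference.

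The conflict between Outcomes and Data Collection Methods, over both groups and variables, can be read directly from the text and needs no assumption.

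The consequence is confined to what the reach analysis can conclude. The comparison is described as descriptive, and the PiH effect estimate does not depend on it.

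**What to change.** - **Selection effects:** compare participants with eligible decliners only, separately for the preimplementation and postimplementation phases, using the participation status and reasons in the eligibility file.
- **Representativeness:** show ineligible patients as a separate descriptive group beside participants and decliners.
- **Consistency:** reconcile Outcomes (Reach), Statistical Methods (Reach), Data Collection Methods and Data Management, so that they agree on which groups are covered, which variables are compared, and whether each comes from R3 or the eligibility file.

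For the eligible-only contrast this needs no new data collection. If ineligible patients are kept, the extract must cover them. Analysis is due to start in August 2026, so the wording can be settled beforehand.

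The cost is a little more analysis and a less precise contrast. For example, for a characteristic present in 50% of each group (assumed), 95 participants against 1155 nonparticipants give a 95% interval of about ±1.96 × √(0.25/95 + 0.25/1155) = ±10 points. At an assumed 50% participation there would be 95 decliners, giving ±1.96 × √(0.25/95 + 0.25/95) = ±14 points. If that rate held in each phase, the intervals would be ±1.96 × √(0.5/42) = ±21 points before and ±1.96 × √(0.5/53) = ±19 points after implementation. The phase-specific results should therefore be reported as estimates with intervals.

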#### RE-AIM: Effectiveness

##### Effectiveness on Health Outcomes of Survivors of Burn Injuries – Coprimary Outcome Measure

Self-management skills: The primary outcome measure is self-management skills, which will be assessed with the revised version of the Partners in Health scale (PiH) [34]. The PiH measures self-management behavior. In the Dutch PiH, two subscales are identified, (1) knowledge and coping, and (2) recognition and management of symptoms and adherence to treatment [46]. Higher scores indicate better self-management skills. Psychometric properties of the PiH scale show good construct validity and reliability. Cronbach α to measure internal consistency varies from 0.82 to 0.86 [34,46,47]. The intraclass correlation coefficient (ICC) to measure test-retest reliability varies from 0.77 in the French version PiH to 0.818 in the Chinese version of the PiH, indicating a good test-retest reliability [48,49]. Although no data have been found on responsiveness, the PiH has shown to provide valid and consistent evidence of self-management skills of patients with chronic conditions [47].

##### Effectiveness on Health Outcomes of Survivors of Burn Injuries – Secondary Outcome Measures

Self-regulation: Currently available self-report measures of self-management among patients with chronic conditions do not address all elements incorporated into the intervention and are generic. Therefore, Mol et al [35] developed a new self-report instrument (Self-Regulation Assessment [SeRA]) based on a model of self-regulation, expert and patient opinions, and cognitive interviews. The SeRA assesses four domains of self-regulation: (1) insight into one’s own health condition, (2) insight into own capabilities, (3) trust in self and apply self-regulation, and (4) organization of help. A higher score on the scale indicates a higher level of self-regulation skills in the context of an organ transplantation. Mol et al [35] showed that the SeRA exhibits high internal consistency (Cronbach α=0.93) and that it is a valid and reliable instrument to assess the necessary self-regulation skills among rehabilitation patients.

Participation: To assess participation, we will use a shortened version of the Measure of Experiential Aspects of Participation [36]. Participants will be asked if they participate in four different life domains, (1) employment, (2) mobility, (3) sport, and (4) exercise. The response options will be used to assess both participation in the activity and the individual’s satisfaction with the level of participation.

Daily activities: Participants will be asked if they can perform their daily activities. This question is part of the EQ-5D-5L questionnaire, which has been shown to have good known-group validity [37,50-52].

Self-care: In addition to daily activities, 1 item of the EQ-5D-5L also assesses self-care [37]. Participants will be asked if they are capable of performing self-care activities.

Dependency: Participants will be asked if they are dependent on other people in their daily lives. This is a newly formulated question.

Return to work or school: This will be assessed by the adjusted International Consortium for Health Outcomes Measurement return to work or school instrument at 6 and 12 months after discharge [38]. Participants will be asked about their daily occupation, with the following response options, (1) “I work 36 hours or more per week,” (2) “I work 35 hours or less per week,” (3) “I am job searching,” (4) “I do not have a paid job (I go to school or am studying),” (5) “I do not have a paid job (retired, volunteer, stay-at-home occupation),” (6) “I cannot work because of my burn injury,” and (7) “I cannot work due to other health issues.” Furthermore, they will be asked if their job has been adjusted since their burn injury (eg, physical adjustments or reduced working hours), with “yes” or “no” as response options. Finally, they will be asked, if relevant, how long after their burn injury they have started working or studying again.

Patient-centeredness: The overall experience of care will be assessed using the Dutch translation of the subscale “patient-centeredness” of the American Consumer Assessment of Health Plan Survey, which consists of 5 questions [39,53]. This scale has been validated for use in the Dutch population and shows good internal consistency (Cronbach α=0.90) [38]. Participants will be asked if they feel listened to by their health care professional, if sufficient time is dedicated to their concerns, if they feel health care professionals take them seriously, if the health care professionals are able to appropriately explain things, and their level of trust in the health care professional’s competence.

##### Health Care Professional Level Outcomes – Secondary Outcome Measures

Self-management support skills: The self-management support skills of the participating health care professionals will be assessed using the Self-Efficacy and Performance in Self-management Support (SEPSS) instrument [40]. The aim of the instrument is to assess self-efficacy and performance in self-management support. The six subscales of the SEPSS are based on the 5 A’s model, (1) assess, (2) advise, (3) agree, (4) assist, (5) arrange, and (6) overall competencies. This questionnaire shows good internal consistency (Cronbach α=0.96) as well as a good test-retest ICC (ICC=0.95).

Need-supportive counseling: The self-management support skills of the participating health care professionals will be objectively evaluated in the preimplementation and postimplementation phases, via video observations using the Coding and Observing Need-Supportive Counseling in Chronic Care Encounters (COUNSEL-CCE) [41]. The survivors of burn injuries and health care professionals who will be filmed will be asked to give consent. Each health care professional will be filmed at least once during the preimplementation and postimplementation phases. The aim of the instrument is to observe need-supportive and need-thwarting counseling in chronic care encounters. The COUNSEL-CCE consists of 44 items divided into nine scales of behavioral approaches, namely (1) participative, (2) attuning, (3) guiding, (4) clarifying, (5) demanding, (6) domineering, (7) abandoning, (8) awaiting, and (9) relatedness supportive reciprocity. The procedure for the observation is the observation of the interaction between the professional and the patient during a 5-minute interval, coding of the observed interval, and observing the same interval for a second time to code any aspects missed. Before scoring the video recordings, the researchers will be trained in the use of the manual, which is provided by the developers of the instrument.

In addition to the COUNSEL-CCE, the video recordings will also be evaluated using the Nurse-Child Interaction Taxonomy (NCIT) [42]. Although this taxonomy was originally developed to improve nurse-child communication, it can also be used to systematically document the interaction between nurses and adult patients. The NCIT consists of 16 elements divided into three main patterns, (1) being considerate, (2) attuning oneself, and (3) procedural intervention.

